##### Early stopping guidelines

An interim futility analysis will be conducted when one-third of patients have had their 6 months follow-ups. If the upper 95% confidence limit of the mean difference in 6-months change scores between the treatment arms is less than the pre-specified non-inferiority margins (*i.e.,* <-6 for GU and <-5 for GI), then the 5-fraction arm will be deemed inferior to the 20-fraction arm and the study will be halted.

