### Statistical analysis

#### Sample size and accrual

The primary objective of this study is to determine if 5 fractions of MRgRT does not increase GI or GU toxicity over 20 fractions of MRgRT. The primary endpoints are change scores in the bowel (GI) or urinary (GU) domains of the EPIC. The change scores will reflect the 2-year score minus the pre-treatment (baseline) score. It is hypothesized that the EPIC mean change score will be no worse in the 5-fraction arm than it is in the 20-fraction arm for both GI and GU toxicity. The sample size is calculated based on a non-inferiority design. The non-inferiority margins are set to be a change score of 6 points for the GI symptoms and 5 points for the GU symptoms. The standard deviation of the change scores are assumed to be 13.2 for the GI symptoms and 10.5 for the GU symptoms based on estimates in the RTOG 0415 trial [29]. This level of change in scores seems to be clinically meaningful. A sample size of 122 with 61 in each arm will provide 80% power for the GI endpoint and 83% power for the GU endpoint to detect non-inferiority using a one-sided, two-sample t-test with 0.05 level significance. Adjusting for a projected 10% EPIC/non-compliance rate, we will accrue and randomize a total of 136 patients (68 per arm). The primary endpoint analysis will occur approximately 4 years after study activation.

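### The interim rule is called a futility analysis but is an inferiority boundary: it rarely stops a trial whose true deficit is up to about 1.5 times the margin, and its thresholds and trigger need to be fixed

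*Protocol article*

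**What the plan says.** The Early stopping guidelines announce the look in these words: "An interim futility analysis will be conducted when one-third of patients have had their 6 months follow-ups". The trigger is that the "upper 95% confidence limit of the mean difference in 6-months change scores between the treatment arms is less than the pre-specified non-inferiority margins", printed as below −6 for GU and below −5 for GI. If it is met, the 5-fraction arm is declared inferior and the study stops.

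The Sample size and accrual section assigns the margins the other way round: "The non-inferiority margins are set to be a change score of 6 points for the GI symptoms and 5 points for the GU symptoms". The SDs of the change scores are "assumed to be 13.2 for the GI symptoms and 10.5 for the GU symptoms". The final test is carried out "using a one-sided, two-sample t-test with 0.05 level significance" for each domain, and the hypothesis is that neither domain is worse in the 5-fraction arm.

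The interim text does not say whether the 95% limit is one- or two-sided, or whether one domain crossing is enough. The article describes no other stopping rule.

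**The concern.** A futility rule stops a trial once success has become unlikely. This rule waits until the interim data, from a third of the patients, place the whole confidence interval on the wrong side of the margin. That is a boundary for established inferiority, and it is far harder to reach. Someone relying on the name would expect a trial heading for failure to be stopped early. For true deficits moderately beyond the margin, it would usually run on.

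Two further faults sit in the same sentence. The thresholds contradict the design margins. The word joining the two domains can also be read as requiring both to cross, although the trial's claim needs non-inferiority in both, so failure in either one defeats it.

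**Working it through.** **Inputs.** From Sample size and accrual: margins 6 (GI) and 5 (GU); SDs 13.2 and 10.5; 61 evaluable patients per arm; one-sided 0.05; 136 randomised. From Early stopping guidelines: one-third of patients at 6 months, 136/3 ≈ 45, or 22.5 per arm. Assumptions: the SDs, planned for 2-year change, also apply at 6 months; a true difference of 0 underlies the stated power; normal approximation.

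**The plan's own figure.** The plan says "A sample size of 122 with 61 in each arm will provide 80% power for the GI endpoint" and 83% for GU. Power ≈ Φ(margin / (SD·√(2/61)) − 1.645).
- GI: 6/2.390 = 2.510, giving Φ(0.865) = 80.7% (80.3% by noncentral t).
- GU: 5/1.901 = 2.630, giving Φ(0.985) = 83.8% (83.4%).

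Both agree with the plan. Swapping the margins would give Φ(5/2.390 − 1.645) = 67% for GI and Φ(6/1.901 − 1.645) = 93% for GU. So 6 for GI and 5 for GU are the margins on which the trial was sized.

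**Deficit needed to stop.** Standard error = SD·√(2/22.5): 3.94 (GI) and 3.13 (GU). Required observed deficit = margin + q·SE.

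| | q = 1.96 (two-sided 95%) | q = 1.645 (one-sided 95%) |
|---|---|---|
| GI, margin 6 | 13.7 (2.29×) | 12.5 (2.08×) |
| GU, margin 5 | 11.1 (2.23×) | 10.1 (2.03×) |

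With the thresholds as printed, GI (5) needs 11.5 to 12.7 points and GU (6) needs 11.1 to 12.1. The lowest multiple of a printed threshold is 1.86 (GU, one-sided). If one-third is taken of the 122 evaluable patients, the two-sided multiples for the design margins rise to 2.35 and 2.29.

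**Chance of stopping, per domain, design margins.** P(stop) = Φ((true deficit − required deficit)/SE). Ranges cover GI and GU.

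| True deficit | Two-sided limit | One-sided limit | Final success in that domain |
|---|---|---|---|
| 1 × margin | 2.5% | 5% | 5% |
| 1.5 × margin | 12% | 19–20% | about 0.2% |
| 2 × margin | 33–36% | 45–48% | about 0% |
| 3 × margin | 86–89% | 92–94% | about 0% |

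**Either or both domains.** These are simulated with domain correlation 0 or 0.5.
- Both domains at 1.5 times the margin: 20–22% (two-sided) or 30–35% (one-sided) stop if either suffices; 1–4% or 4–8% if both must cross.
- Both domains at twice the margin, two-sided: 50–57% if either suffices, 12–19% if both must cross.
- GI alone at twice the margin, GU equal: the either reading stops at least as often as GI alone, 33–45%. The both reading cannot exceed the chance that GU crosses, Φ(−11.14/3.13) = 0.02% (two-sided) or Φ(−10.15/3.13) = 0.06% (one-sided), so it is about 0%.

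**False stops when the arms are equal, either domain.** Adding the two domains: two-sided 0.025% + 0.019% ≈ 0.04%; one-sided 0.076% + 0.059% ≈ 0.14%.

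**The case against.** The strongest reply is that a strict boundary is a legitimate choice here. The interim uses 6-month scores while the co-primary endpoints are 2-year changes, and the article's Discussion distinguishes acute from late effects. An early deficit might resolve, and a looser rule would then stop a trial that could have succeeded. This stands, and it can be sized. Suppose a 6-month deficit equal to the margin in both domains resolves fully by 2 years, with an assumed within-patient correlation of 0.6. A one-sided 80% limit in either domain would stop 31–36% of such trials and lose about 18–20 points of joint power. The 95% limit in either domain would lose about 2 points, or 4–5 if one-sided. The cost of about 0.6 points for the 80% limit applies only if the arms are equal throughout. A reader might infer that loosening the limit is nearly free; these figures do not support that.

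A reader might also infer that the rule almost never stops a failing trial. That fits only deficits at or near the margin. At twice the margin it stops a third to a half of the time per domain, and at three times it usually stops.

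Nor does the article show that the trial has no other safeguard. It is a condensed account, CTCAE grading is scheduled at every visit, and the full protocol may hold other monitoring rules. Operating characteristics may also be given there, so their absence from the article is not held against it.

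None of this answers the mismatch between name and rule, the reversed thresholds, or the unstated trigger. The article writes all of these out itself.

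**Conclusion.** The concern holds in a limited form. The rule is a harm boundary under a futility label, and it does not give the protection the label promises. With the design margins it needs an observed deficit of about 2.0 to 2.3 times the margin. It rarely stops a trial whose true deficit is up to about 1.5 times the margin, where final success is already about 0.2% per domain. The strictness itself is permissible. The faults are the name, thresholds that contradict the sample size section, and silence on the trigger and on the sidedness of the limit. The trigger matters most: with GI alone failing at twice the margin, it decides between stopping about 0% and 33–45% of trials.

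The figures assume that the 2-year planning SDs hold at 6 months and that about 45 patients contribute. A larger SD or fewer patients raises the required deficit; a smaller SD lowers it. Under the printed thresholds the multiples shift somewhat (1.86 at the lowest), but the nature of the rule does not change.

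**What to change.** In the Early stopping guidelines:
- Name the rule an inferiority or harm boundary.
- Reconcile its thresholds with Sample size and accrual: −6 for GI and −5 for GU, the margins that reproduce the stated power.
- State that crossing in either domain triggers it.
- State whether the 95% limit is one- or two-sided.

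This changes wording only. When the arms are equal, the chance of a false stop is about 0.04% (two-sided) to 0.14% (one-sided).

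If futility protection is really intended, add a separate, non-binding rule based on conditional power for the 2-year test. Its operating characteristics should include an early deficit that resolves by 2 years. A one-sided 80% limit on the 6-month scores is an alternative to weigh. With both domains truly at 1.5 times the margin it would stop 64–73% of trials, against 20–22% for the two-sided 95% limit in either domain. The price is about 0.6 points of joint power if the arms are equal throughout, and about 18–20 points in the transient-deficit case described above.

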#### Data analysis

##### Analysis of primary endpoints

The co-primary endpoints are GI and GU toxicity as measured by the bowel and urinary EPIC domains, respectively. The change scores, calculated as baseline score subtracted from 2-year score, will be analyzed using a non-inferiority t-test based on the prespecified non-inferiority margins with a significance level of 0.05. If the data are determined to be non-normal, a Wilcoxon test may be used instead. All patients with EPIC bowel and urinary domain scores will be included in the primary endpoint analysis. The EPIC scoring manual will be followed which requires ≥ 80% of items in a domain to be completed in order to obtain a score for that domain.

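### The interim futility rule joins the bowel and urinary limits with 'and' and does not say whether one domain is enough; read literally, both must cross, which does not fit a hypothesis that requires non-inferiority in each

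*Protocol article*

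**What the plan says.** Three places in the protocol article bear on this.

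- **Early stopping guidelines.** The single interim look is described as follows: "An interim futility analysis will be conducted when one-third of patients have had their 6 months follow-ups". The criterion begins "If the upper 95% confidence limit of the mean difference in 6-months change scores between the treatment arms is less than" the pre-specified margins. A parenthesis introduced by 'i.e.' then spells the margins out and leads to one verdict on the arm: "<-6 for GU and <-5 for GI), then the 5-fraction arm will be deemed inferior". The study is then halted. The sentence contains neither 'either', 'respectively' nor 'in each domain'.
- **Sample size and accrual.** The hypothesis is that the mean change score is "no worse in the 5-fraction arm than it is in the 20-fraction arm for both GI and GU toxicity". The margins are "a change score of 6 points for the GI symptoms and 5 points for the GU symptoms", and the standard deviations are "assumed to be 13.2 for the GI symptoms and 10.5 for the GU symptoms".
- **Analysis of primary endpoints.** "The co-primary endpoints are GI and GU toxicity as measured by the bowel and urinary EPIC domains, respectively".

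Nothing else in the article says how the two domains combine at the interim look.

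**The concern.** Success requires non-inferiority in the bowel domain and in the urinary domain. The logical opposite is inferiority in at least one of them. A futility rule that serves this hypothesis should therefore respond when either domain crosses. The printed conjunction, taken at its word, responds only when both cross at the same look.

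At stake is what happens if the 5-fraction schedule produces a large excess in one organ system and little in the other. A monitoring group applying the sentence literally would let accrual continue. A group reading it as two separate domain checks would halt. The same data could thus lead to opposite decisions, and the text does not settle which one applies.

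**Working it through.** **Inputs.** Margins 6 (GI) and 5 (GU), standard deviations 13.2 and 10.5, 61 evaluable per arm and 136 randomized, all from Sample size and accrual. The interim takes place at one-third of patients: 136/3 ≈ 45, taken as 22 and 23 per arm.

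**1. The plan's own figures reproduce.** The test is stated as "using a one-sided, two-sample t-test with 0.05 level significance". With no true difference and 61 per arm:
- GI: SE = 13.2·√(2/61) = 2.39; 6/2.39 − 1.645 = 0.865; power 80.7% (80.3% with the noncentral t), against 80% stated.
- GU: SE = 10.5·√(2/61) = 1.90; 5/1.90 − 1.645 = 0.985; power 83.8% (83.4% with the noncentral t), against 83% stated.
- 122/0.9 = 135.6, rounded up to 136.

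So the margins and standard deviations are the ones the design was built on.

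**2. Interim boundary per domain.** The difference is 5-fraction minus 20-fraction, with a two-sided 95% limit and the normal approximation. The limit lies below −margin when the observed difference is below −(margin + 1.96·SE).
- GI: SE = 13.2·√(1/22 + 1/23) = 3.94; boundary −(6 + 1.96·3.94) ≈ −13.7.
- GU: SE = 10.5·√(1/22 + 1/23) = 3.13; boundary −(5 + 1.96·3.13) ≈ −11.1.

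**3. Probability that a domain crosses.** For a true deficit d this is Φ((d − boundary size)/SE).

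| True deficit d | GI crosses | GU crosses |
|---|---|---|
| 0 | Φ(−3.48) = 0.02% | Φ(−3.56) = 0.02% |
| 10 | Φ(−0.94) = 17% | Φ(−0.36) = 36% |
| 15 | Φ(0.33) = 63% | Φ(1.23) = 89% |

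**4. Combining the domains when only one has a deficit.** Under 'either', the stopping probability is essentially that of the affected domain: 17% or 36% at 10 points, 63% or 89% at 15 points. Under 'both', it cannot exceed the crossing probability of the unaffected domain, which is about 0.02%. This bound holds whatever the correlation between the domains.

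**5. Cost of 'either' in false stops.**
- No true difference: at most 0.025% + 0.019% ≈ 0.04%.
- Both true differences exactly at the margins: each domain crosses with probability 2.5%, so under independence 1 − 0.975² = 4.9%. Simulation with correlation 0.5 gives 4.6%. Under 'both' the figures are 0.06% to 0.4%.

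**6. Sensitivity.**
- The interim parenthesis pairs 6 with GU and 5 with GI, the reverse of the design. With those values the boundaries are about −12.7 (GI) and −12.1 (GU). A one-domain deficit of 15 points then stops with probability 72% (GI) or 82% (GU) under 'either', and one of 10 points with about 25% in each. 'Both' stays below 0.1%, and a false stop with no difference is about 0.07%.
- With t limits and 22 per arm, a 15-point bowel-only deficit stops in 60% of simulated trials under 'either' and in at most 0.03% under 'both'.
- If the limit is one-sided 95%, the same scenario gives 72% against at most 0.07%.

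**The case against.** **The 'and' may only be a list.** It sits inside an 'i.e.' parenthesis that spells out two domain-specific margins. Sample size and accrual uses the same construction where it plainly means 'respectively', as in "a change score of 6 points for the GI symptoms and 5 points for the GU symptoms". A domain-by-domain check fits the sentence about as well. This stands: a reader might infer that the trial has chosen a rule that ignores single-domain inferiority, and the text does not support that. It shows an ambiguity whose literal reading runs against the hypothesis. A stopping rule should not depend on guessing the intent, and either reading calls for the same edit.

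**Six months is not two years.** A reader might also infer that, after a crossing in one domain, the trial could no longer meet its hypothesis. That goes too far. The interim uses 6-month change scores in about 45 patients, whereas the hypothesis concerns the 2-year change. Still, the rule itself takes a 6-month crossing as enough to deem the arm inferior and halt, so how the domains combine matters on the rule's own terms.

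**The domains may move together.** It is tempting to cite the comparison of MRI with CT guidance in post-prostatectomy SBRT (Background), where acute GI toxicity differed and GU did not. That comparison was non-randomized, used CTCAE grades and did not concern fractionation, and its late GI difference was not significant. The randomized comparison in intact prostate cancer described beside it found GI and GU falling together. The article does not establish how the domains will behave here, and the point does not rest on it.

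**The scenarios are extreme.** Deficits of 10 and 15 points come from nowhere in the article. The preliminary phase III results in the Background imply between-schedule differences of about 5.2 − 0.3 = 4.9 (GU) and 2.2 − 1.5 = 0.7 (GI). A true GU deficit of 4.9 crosses with probability Φ((4.9 − 11.1)/3.13) ≈ 2%. For deficits of that size neither reading stops often, so the wording matters only for large one-domain deficits.

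**Other monitoring exists.** CTCAE is recorded at every visit, and the full protocol may say more. That is fair, and no claim is made that toxicity would go unobserved. The point concerns only the rule as stated.

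**Conclusion.** The point holds as a defect of wording with a real but bounded consequence. The interim rule leaves open whether one domain suffices, and its literal reading does not match a hypothesis that inferiority in either domain counts against. Under that reading, a deficit confined to one domain almost never stops the trial (below 0.1%). Under 'either', the probability is about 17% (GI) or 36% (GU) for 10 points and 63% or 89% for 15 points.

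These figures assume 22 and 23 patients with complete EPIC data, the standard deviations assumed for the 2-year change holding at 6 months, a two-sided 95% limit, the design margins, no deficit in the other domain, and illustrative effect sizes. The contrast between the readings survives t limits, a one-sided limit and the margins as printed in the interim rule. The wording should be corrected before the interim look.

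**What to change.** Replace the criterion under Early stopping guidelines with wording such as: *The futility criterion is met if, in either the bowel or the urinary domain, the upper 95% confidence limit of the difference in mean 6-month change score (5-fraction minus 20-fraction) lies below the negative of that domain's pre-specified non-inferiority margin.* The verdict should then name the domain in which the arm is deemed inferior.

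In the same edit, reconcile the margins printed in the interim rule (6 for GU, 5 for GI) with those under Sample size and accrual (6 for GI, 5 for GU). This is a separate contradiction in the same sentence, and correcting it alone would leave the 'and' in place.

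The cost is one sentence. The sample size and the final analysis are unchanged. With no true difference the false-stop probability under 'either' stays below 0.1%; with both true differences exactly at the margins it is about 5%. Stopping for inferiority cannot raise the type I error of the non-inferiority claim.

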### Evaluation of randomization and blinding

This study will employ a randomized phase II non-inferiority design to compare 5 fractions of ultra-fractionated MRgRT versus 20 fractions of moderately hypofractionated MRgRT in the salvage setting for prostate cancer patients after prostatectomy. Patients will be stratified according to baseline EPIC bowel and urinary domain scores (*i.e.,* high bowel score and high urinary score vs. high bowel score and low urinary score vs low bowel score and high urinary score vs. low bowel score and low urinary score) as well as pelvic radiotherapy and androgen therapy (*i.e.,* yes vs. no), for these factors are expected to be associated with the primary outcome. Within each strata, patients will be randomized 1:1 to receive 5 fractions or 20 fractions using permuted block randomization. The trial schema is displayed in Fig. 1.

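### The interim halting rule prints the GI and GU non-inferiority margins transposed relative to the sample-size section

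*Protocol article*

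**What the plan says.** Three places in the protocol article bear on this.

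- **Sample size and accrual** fixes the margins: "The non-inferiority margins are set to be a change score of 6 points for the GI symptoms and 5 points for the GU symptoms". The SDs of the change scores are "assumed to be 13.2 for the GI symptoms and 10.5 for the GU symptoms". The design claim is "A sample size of 122 with 61 in each arm will provide 80% power for the GI endpoint and 83% power for the GU endpoint", "using a one-sided, two-sample t-test with 0.05 level significance". The hypothesis is that the "EPIC mean change score will be no worse in the 5-fraction arm than it is in the 20-fraction arm", and it is stated for both domains.
- **Analysis of primary endpoints** gives no numbers for the margins and points back to the prespecified ones.
- **Early stopping guidelines** sets one interim look, when a third of patients have reached 6 months. The trigger is an upper 95% confidence limit for the between-arm difference in 6-month change scores that lies below the pre-specified margins. These are then spelled out as "<-6 for GU and <-5 for GI". Crossing means that the 5-fraction arm is declared inferior and the trial is halted.

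Change scores are follow-up minus baseline, so a more negative difference is worse for the 5-fraction arm.

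**The concern.** The interim rule presents its two numbers as the margins already set, not as separate interim margins, yet they are attached to the opposite domains. Nothing in the article defines or justifies a different interim pair. Both statements are current text, so a reader cannot apply one without contradicting the other.

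This is the only early stopping rule in the document, and its consequence is to halt the trial. If it were applied as printed, urinary harm would be judged against a threshold one point more extreme than the trial's own margin, and bowel harm against one a point less extreme. The trial could then continue, or be halted, on a threshold that the final analysis does not use.

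**Working it through.** **Step 1. Which pairing does the design calculation use?**

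Inputs, all from the sample-size section: 61 per arm, one-sided alpha 0.05, two-sample t-test, SD 13.2 (GI) and 10.5 (GU). The true difference is taken as 0, the usual reading of the no-worse hypothesis.

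SE = SD × √(2/61), which is 2.390 for GI and 1.901 for GU. Power is the probability that a noncentral t variable with 120 degrees of freedom and noncentrality margin/SE exceeds the critical value 1.658.

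| Domain | Margin | Margin/SE | Power (t) | Normal approximation | Stated |
|---|---|---|---|---|---|
| GI, sample-size pairing | 6 | 2.510 | 80.3% | 80.7% | 80% |
| GU, sample-size pairing | 5 | 2.630 | 83.4% | 83.8% | 83% |
| GI, interim pairing | 5 | 2.092 | 66.8% | 67.3% | 80% |
| GU, interim pairing | 6 | 3.156 | 93.2% | 93.5% | 83% |

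The inflation also reproduces: 122/0.9 = 135.6, rounded up to 136. The sample-size section is internally consistent with GI 6 and GU 5. The interim pairing matches neither stated power.

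**Step 2. What does the transposition do to the interim rule?**

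Assumptions, because the article does not give these figures: one-third is taken of the 136 randomised, so 136/3 = 45.3 patients, or about 22.7 per arm; the planning SDs for the 2-year change also hold at 6 months; each domain is looked at on its own. The article does not say whether the 95% limit is one- or two-sided, so both are shown.

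SE = SD × √(2/22.67), which is 3.92 for GI and 3.12 for GU.

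Crossing needs an observed difference below -margin - z × SE, with z = 1.96 (two-sided limit) or 1.645 (one-sided limit). With a true difference d, P(cross) = Φ((-margin - z × SE - d)/SE).

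Observed difference needed, two-sided limit:

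- GI: -6 - 1.96 × 3.92 = -13.7 with its own margin; -12.7 as printed.
- GU: -5 - 1.96 × 3.12 = -11.1 with its own margin; -12.1 as printed.

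Worked case, GU at d = -10, two-sided: as printed, (-12.11 + 10)/3.12 = -0.68, so 25%; with its own margin, (-11.11 + 10)/3.12 = -0.36, so 36%.

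| True difference | Limit | As printed | Own margin |
|---|---|---|---|
| GU -10 (twice its margin) | two-sided | 25% | 36% |
| GU -10 | one-sided | 36% | 48% |
| GI -12 (twice its margin) | two-sided | 43% | 33% |
| GI -12 | one-sided | 56% | 45% |
| GU -5 (at its margin) | two-sided | 1.1% | 2.5% |
| GI -6 (at its margin) | two-sided | 4.4% | 2.5% |

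**Step 3. Sensitivity.** Taking one-third of the 122 evaluable patients instead (20.3 per arm, two-sided limit) gives GU at -10 of 23% against 33%, and GI at -12 of 39% against 30%. Using t in place of normal quantiles at 22.7 per arm (two-sided) gives GU at -10 of 23% against 34%. The direction does not change in any of these.

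**The case against.** **The effect is modest.** Each threshold moves by one point, where the observed difference needed is 11 to 14 points. At a domain's own margin the crossing probability moves by only 1.4 to 1.9 percentage points. The two errors also pull in opposite directions: if both domains were at twice their margins, either crossing stopped the trial and the domains were independent, the overall stop probability would be about 57% with either pairing. All of this stands. The shift of about 10 points per domain matters mainly when one domain is harmed and the other is not. That is still no reason to leave a wrong threshold in a halting rule.

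**The article condenses a full protocol that is not shown.** This stands as a limit. The operative document may carry the right pairing, so the claim is that the trial could be judged on the wrong thresholds, not that it will be.

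**A reader might infer that both domains must cross before the trial stops**, because the two thresholds are joined by a conjunction. The text does not establish this. The parenthesis can equally be read as listing one margin per domain. It is an ambiguity to clear up, not a demonstrated defect. It is worth clearing up because the joint reading would leave harm confined to one domain almost undetected: with GU at -10 and GI at 0, both would cross less than 0.1% of the time.

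**A reader might also infer that the rule is practically unreachable, or that a futility look should use a looser trigger such as the point estimate.** The figures do not support the first: with matched margins the crossing probability at twice the margin is 33% to 36% (two-sided) or 45% to 48% (one-sided). The second is a design preference. The rule concludes inferiority when crossed, and a strict bound on 6-month data for a 2-year endpoint is a defensible choice even if the word futility is loose. A point-estimate trigger would also signal a false stop in about 6% of trials per domain at no true difference, or about 12% in at least one if the domains are independent.

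**Conclusion.** The contradiction is certain and needs no assumption beyond the text: the same two margins are attached to opposite domains in two sections. The article's own power figures identify the interim rule as the misprinted one.

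The size is moderate and conditional. It rests on about 22.7 patients per arm at the look, the 2-year SDs holding at 6 months, and each domain being considered separately. Under those, harm at twice the margin is caught about 11 to 12 percentage points less often for GU, and about 10 points more often for GI, than the trial's own margins imply.

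The final test, its significance level and the sample size are untouched, since the primary analysis refers to the prespecified margins. The point should be corrected because a halting rule must carry the right thresholds, not because the design fails without it.

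**What to change.** Reconcile the early stopping guidelines with the sample-size section, so that the interim thresholds read: upper 95% confidence limit below -6 for GI, below -5 for GU. In the same sentence, state that crossing in either domain triggers the rule, which follows from a hypothesis that requires non-inferiority on both. If a different interim pair was in fact intended, it should be labelled as such and justified, and no longer described as the pre-specified margins.

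The full protocol and any monitoring documents should be checked for the same transposition. The cost is a wording correction, with no change to sample size, timing or the final analysis.
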